### Dosage of medicines to be used

Infants randomised to the intervention arm will receive the first dose of oral amoxicillin in the hospital at discharge. Those randomised to the control arm will be in the hospital and receive injectable antibiotics (**Table 4**).

**Table 4 T4:** Treatment arms

	Continuation of hospital treatment arm		Home arm
	Injection gentamicin	Injection ampicillin	Oral amoxicillin
Route	IM / IV	IM / IV	Oral
Frequency (per day)	Once	Two-four*	Twice
Dose by weight	Strength, 40 mg / ml	Strength 250 mg / 1.5 ml	250 mg dispersible tablet
1.5-2.4	0.2	0.8	1 / 2 tablet
2.5-3.9	0.4	1.2	1 / 2 tablet
4.0-5.9	0.6	1.5	1 tablet
Duration	Continue for a further 5 days (total 7 days)	Continue for a further 5 days (total 7 days)	Stop injections and start oral amoxicillin for 5 days

IM – intramuscular, IV – intravenous, mg – milligramme, ml – millilitre

*Depending on the age of the child, see [4], for the hospitalised child, twice daily in the first week of life, thrice daily in 2-4 weeks of life, four times daily in 4+ weeks of life.

### Treatment documentation

The study treatment documentation and compliance team will document the treatment received in the hospital (control) and home (intervention) from days one to seven after enrolment. For infants in the control arm, the documentation of treatment received will be captured from the hospital inpatient treatment charts. For infants in the intervention arm, the documentation of treatment received will be captured through mother reports or physicians' outpatient department (OPD) records.

### Outcome assessment

Due to the nature of the treatment, the trial cannot be blinded. To reduce potential measurement bias, we will use Independent Outcome Assessors (IOA) who will not be associated with the treatment of the infant. The IOAs who will be the Outcome Assessment Team members will conduct outcome assessment visits using the designated days four, eight and 15 post-admission. In the hospital arm, the outcome visits on day four will be done in the hospital, while on days eight and 15, visits will be done at home (or in the hospital or where ever the infant may have moved to). In the outpatient arm, the outcome visits on days four, eight, and 15 will be done at home or where ever the infant may have moved to. If the infant is not able to be seen on the specified day, then a window of additional time will be allowed for outcome follow up, i.e. for day four visit, an additional 24 hours; for day eight and day 15 visits, an additional 48 hours. The outcome team will continue to visit the family during this time window to complete these visits.

Outcomes will only be ascertained by the IOAs per the criteria mentioned above under outcomes. A case will be considered to have a poor clinical outcome if it is confirmed by the IOA.

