### Outcomes

The primary outcome is “poor clinical outcome” defined as 1) death between randomisation (day three of initiation of therapy) and day 15 of initiation of therapy, or 2) presence of any sign of critical illness (no movement at all, unable to feed at all, or convulsions) or any sign suggestive of another serious infection, e.g. meningitis, bone or joint infection, on day four and eight of initiation of therapy, or 3) presence of any sign of CSI on day eight of initiation of therapy.

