Treatment provision (control arm)	Continue hospitalisation for injectable antibiotics and supportive care	Hospital / study staff	After enrolment, consent and randomisation	Hospital	Giving injectable therapy
Treatment documentation	Follow-up for treatment documentation	Treatment documentation team	Days 4, 8 of initial admission	Intervention arm: patients' homes or OPD	Intervention arm: asking mothers and checking medicine bottles
				Control arm: hospital where the patient is admitted	Control arm: hospital inpatient treatment records
Supervision	Sub-sample on follow-up days for quality assurance	Study supervisor	Days 4, 8 and 15 of initial admission	Intervention arm: patients’ homes and OPD	Verification and substantiating assessment
				Control arm: hospital where the patient is admitted and patients’ homes	
Outcome assessment	Outcome assessment	Independent Outcome Assessment Team	Day 2, 4, 8, 15 post-randomisation and if the patient deteriorated in between	Intervention arm: patients’ homes or a hospital if the patient was admitted	Clinical assessment and filling outcome assessment form
				Control arm: hospital where the patient is admitted and at home after discharge	

OPD – outpatient department, CRP – C-reactive protein, CRF – case report form, WHO – World Health Organization

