Our study has several strengths. First, a multi-centre trial in several African and Asian sites with a fairly large sample size from diverse populations will provide precision and generalisability. Second, this trial is being conducted in collaboration with the local governments, which will facilitate future policy adoption if required. Third, standardised training, supervision, oversight, and monitoring will be undertaken to ensure quality, consistency, harmonised trial procedures and implementation. Documentation of treatment and follow-up will be carried out by trained study staff. Investigators will ensure that the protocol and standard operating procedures are followed, data is accurately collected, and the highest level of safety is provided. Outcome assessment by an independent assessor will minimise ascertainment bias. Fourth, enrolment of self-referred babies to the hospitals minimises selection bias. Finally, in addition to regular site monitoring visits by study staff and investigators, the WHO monitoring and coordinating team in Geneva will be engaged to assist with close external monitoring of the study, including regular site monitoring visits to assess compliance with human subjects, other research regulations and guidelines, adherence to the study protocol and procedures, quality and accuracy of data collected, and quality of care and child safety.

The study has some limitations. First, enrolled children will be clinically diagnosed using WHO PSBI guidelines without using microbiological and / or radiological methods. While microbiological and / or other diagnostic aids may add improved specificity to the clinical diagnosis of PSBI, good quality microbiological services are a challenge in most hospitals in LMICs and would limit the generalisability of the study. Second, blinding of intervention therapy is not possible. Third, there may be an element of subjectivity involved in the assessment of poor clinical outcomes based on the presence or absence of clinical signs. To reduce this bias, independent assessors will conduct outcome assessments in both intervention and control arms. Finally, a question may arise about the generalisability of the results because we will be strengthening hospital-based care in the study facilities from an ethical standpoint, which may be different from other facilities that will not get such support.

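### Independence from treatment is the stated answer to an unblindable trial, although partial masking of the day-8 sign reading looks feasible and cheap

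*Protocol article*

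**What the plan says.** All places are in the protocol article.

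- **Outcome assessment** opens with "Due to the nature of the treatment, the trial cannot be blinded". Against measurement bias it continues: "we will use Independent Outcome Assessors (IOA) who will not be associated with the treatment of the infant". It does not mention keeping the allocation from these assessors. It also says that only they ascertain outcomes and that a poor clinical outcome requires their confirmation.
- **Place of visits**, same section. For controls on day 4: "In the hospital arm, the outcome visits on day four will be done in the hospital". Their two later visits have home as the default and other places as fallback: "while on days eight and 15, visits will be done at home (or in the hospital or where ever the infant may have moved to". The intervention arm has the home default at all three visits, again with a fallback if the family has gone elsewhere: "In the outpatient arm, the outcome visits on days four, eight, and 15 will be done at home or where ever the infant may have".
- **Table 2**, outcome assessment row: "Control arm: hospital where the patient is admitted and at home after discharge".
- **Outcomes**: besides death and signs of critical illness or another serious infection, the primary outcome counts "presence of any sign of CSI on day eight of initiation of therapy". Signs of clinical severe infection (CSI) count on that day only.
- **Discussion**, limitations: it states that the therapy cannot be blinded, and then that "there may be an element of subjectivity involved in the assessment of poor clinical outcomes based on the presence or absence of clinical signs". The remedy given is again independent assessors. The strengths paragraph says that independent assessment will minimise ascertainment bias.

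**The concern.** Whether a treatment can be blinded and whether an outcome reading can be masked are separate questions. The article answers the first and moves straight to independence, which is a different safeguard. An assessor with no role in care may still know whether the infant went home on day 3 or stayed in hospital, and may expect one arm to do better or worse. Some CSI signs, such as feeding less well, moving only on stimulation or chest indrawing, rest on clinical judgement, where expectation can tip a borderline call.

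In a non-inferiority comparison, under-reading signs in the home arm lowers the observed relative risk and favours a false conclusion of non-inferiority. Over-reading them, for instance because home care is thought risky, hides true non-inferiority. Either error would act on the result that is meant to inform a change in guidance.

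**Working it through.** **1. Is a masked day-8 reading feasible under the article's own schedule?**

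| Visit | Control arm | Intervention arm | Does place reveal the arm? |
|---|---|---|---|
| Day 4 | hospital | home | yes |
| Day 8 | home by default; hospital or elsewhere as fallback | home by default | not for discharged infants |
| Day 15 | home by default | home by default | not for discharged infants |

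Treatment received is recorded by a separate team (Table 2; Treatment documentation), so the day-8 assessor does not need the arm for that purpose. Infants are randomised only when free of all CSI signs, so a CSI sign on day 8 is a new judgement. Place alone therefore does not rule out masking on day 8 for infants already discharged.

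**2. Inputs for an illustration**

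- From Abstract and Sample size: 2625 per arm, 10% loss, margin RR 1.40, one-sided alpha 0.025, control incidence 5% and 7.5%.
- n = 2625 × 0.9 = 2362 per arm.
- Assumed, since the article gives neither: the share *s* of events that are sign-based and misreadable, and the fraction *m* of those missed in the home arm.

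**3. The article's own figures first.** Power with equal true rates p and margin 0.40p on the risk-difference scale is Φ(0.40p / √(2p(1−p)/n) − 1.96).

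- p = 0.05: Φ(0.0200/0.00634 − 1.96) = 88.4%. Table 3 gives 88.4%.
- p = 0.075: 97.5%. Table 3 gives 97.5%.

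This confirms n and the error rate. The illustration uses the log relative risk because the margin is stated as a relative risk. On that scale, power without reading error is 75.6% and 90.9%.

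**4. Under-reading in the home arm, true RR = 1.40**

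- Observed home-arm rate: pt = 1.40 × pc × (1 − s·m).
- SE = √[(1−pc)/(n·pc) + (1−pt)/(n·pt)].
- P(upper 95% limit < 1.40) = Φ[ln(1.40·pc/pt)/SE − 1.96].

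Worked case: pc = 0.05, s = 0.5, m = 0.10, so s·m = 0.05. Then pt = 0.07 × 0.95 = 0.0665, observed RR = 1.33, SE = 0.1183, ln(1.40/1.33) = 0.0513, and Φ(0.434 − 1.96) = Φ(−1.526) = 6.3%.

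| s | m | Observed RR | False non-inferiority, pc = 5% | pc = 7.5% |
|---|---|---|---|---|
| any | 0 | 1.40 | 2.5% | 2.5% |
| 0.5 | 10% | 1.33 | 6.3% | 7.8% |
| 0.5 | 20% | 1.26 | 14.0% | 19.3% |
| 1 (upper bound) | 10% | 1.26 | 14.0% | 19.3% |
| 1 (upper bound) | 20% | 1.12 | 44.1% | 61.4% |

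The last two rows apply the error to every home-arm event, deaths included.

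**5. Over-reading in the home arm, equal true rates.** With pt = pc × (1 + s·m), pc = 5% and s = 0.5, m = 10% or 20% lowers log-RR power from 75.6% to 63.2% or 49.5%. On the risk-difference scale it falls from 88.4% to 77.9% or 63.7%.

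**The case against.** The case against has real force on several points.

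- *The article never says that assessors cannot be masked.* Correct. The Discussion limits the statement to the therapy, and a condensed article may leave rosters and form content to the full protocol or the manual of operations. Silence on those details is no finding. What remains is the stated position: unblindable treatment answered by independence alone, twice, as the remedy for a conceded subjectivity.
- *Day 4 reveals the arm before day 8.* A reader might infer that one person makes both visits. The text does not say so. It speaks of assessors in the plural, as members of a team, and nothing excludes rotation.
- *Masking would often fail.* This stands in part. Home on day 8 is only the default, and the Discussion also mentions assessing admitted controls in hospital. Families may disclose, and day 8 comes directly after a seven-day course. The assessors also see infants who deteriorate between visits (Table 2), document serious adverse events (Adverse events) and may hear of adverse events at home (Follow-up). It would go too far to say that the reading is unmasked without need.
- *The outcome is less subjective than it looks.* Three of the six CSI signs in Box 1 (high temperature, low temperature, fast breathing) are measured, and death is objective. This is why the error should be applied to only part of the events.
- *Other safeguards exist.* There is quarterly standardisation of assessors on signs, supervisor verification of a sub-sample on days 4, 8 and 15, video checks of signs and observation by investigators. These limit reading error in general but do not remove error that depends on knowing the arm.

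A conflict between the Outcome assessment section and Table 2 on where controls are seen might also be suspected. There is none: hospital while admitted and home after discharge fits home by default on day 8.

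**Conclusion.** The point holds as a worthwhile, inexpensive improvement. The article protects a partly subjective, sign-based primary outcome by independence, standardisation and supervision, none of which withholds the arm from the assessor. Its own schedule leaves room for partial masking on day 8 among discharged infants.

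The size cannot be known from the article. If half of events are misreadable and 10% or 20% of those are missed in the home arm, false non-inferiority at a true RR of 1.40 rises from 2.5% to about 6% or 14% (5% control incidence) and about 8% or 19% (7.5%). The figures of 14% and 44%, and 19% and 61%, are upper bounds that let deaths be misread too. All miss rates are assumptions, and the direction of any bias is open. A reader might infer that the trial is biased towards non-inferiority; nothing in the article shows that.

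**What to change.** In Outcome assessment:

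- State that the day-8 assessor is masked to allocation where practicable.
- Leave the arm off assessors' visit lists and outcome forms.
- Where the existing team allows, assign the day-8 visit to a member who did not make that infant's day-4 visit.
- Examine signs before any treatment history is taken, and ask caregivers beforehand not to say where the infant was treated.
- Record on the form whether the arm became known, and when.

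In the Discussion, say that independence and standardisation reduce expectation bias but do not remove it, in place of the claim that independent assessment minimises it.

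The cost is rostering, a form item and a short caregiver script. It needs no added participants or visits and no change in treatment. The drawback is that masking stays partial: infants still admitted cannot be masked, some families will disclose, safety duties will unmask some assessors, and rotation may be hard at small sites.

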### Follow-up

All infants will be followed up till day 15 after the initial admission. Infants in the intervention arm will be asked to return to the hospital for treatment and assessment by the hospital physician / nurse on day five of treatment initiation. Infants will be assessed for the presence of any adverse event during scheduled follow-up visits to the hospital OPD, hospital visits by the family for care-seeking at any time during the follow-up period, or reported to the IOA team during a home visit and referred for care. These will be managed by the treating physician as per routine practice and followed up till resolution.

Infants in the control arm will be followed up and managed as per routine hospital procedures.

All efforts will be made to follow all the enrolled young infants in both studies. If a young infant does not come to the hospital / health facility on the follow-up day, the study team will contact them by phone and counsel parents / caregivers to bring the infant to the hospital / health facility. Transportation costs will be provided to families of all patients if needed.

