### Adverse events – documentation, reporting and response

Any adverse event that occurs after enrolment will be recorded on an adverse event reporting form by the treating nurse / physician. In case of an SAE, the study staff will contact the study supervisor and IOA. The IOA will document the SAE and convey the information to the study coordinator / investigator. An SAE, like death, anaphylactic reaction, severe diarrhoea, and a disseminated or severe rash will be reported to WHO within 48 hours of the occurrence. These cases will be (except, of course, the ones who unfortunately die) provided appropriate treatment and will be followed up. In case of other minor adverse effects, such as mild rash etc., the treatment will be continued. WHO will periodically report SAEs to the DSMB.

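### Non-fatal adverse events are collected by different routes and with different intensity in the two arms, so any between-arm tabulation of them is open to detection bias of unknown direction

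*Protocol article*

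**What the plan says.** Four parts of the protocol article bear on this.

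- **Follow-up, home arm.** "Infants in the intervention arm will be asked to return to the hospital for treatment and assessment by the hospital physician / nurse on day five" (counted from the start of therapy).
- **Follow-up, adverse-event routes.** "Infants will be assessed for the presence of any adverse event during scheduled follow-up visits to the hospital OPD", at visits the family makes to seek care, or when an event is reported to the independent assessors at a home visit. The next paragraph turns to the comparator: "Infants in the control arm will be followed up and managed as per routine hospital procedures".
- **Adverse events – documentation, reporting and response.** One rule covers both arms: "Any adverse event that occurs after enrolment will be recorded on an adverse event reporting form by the treating nurse / physician". For serious events, study staff notify the supervisor and the independent outcome assessor (IOA), and then "The IOA will document the SAE and convey the information to the study coordinator / investigator". Named serious events go to WHO within 48 hours, and WHO reports serious events periodically to the DSMB.
- **Outcome assessment.** Independent assessors visit both arms on days 4, 8 and 15, with the same time windows. For the control arm: "In the hospital arm, the outcome visits on day four will be done in the hospital, while on days eight and 15, visits will be" at home or wherever the infant is. Only these assessors ascertain the study outcomes.

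The Data analysis section compares poor clinical outcome between arms. It names no adverse-event comparison.

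**The concern.** The recording rule is common to both arms, but the opportunity to apply it is not. A control infant stays in a ward with the people who fill in the form. A home-arm infant meets them once by schedule and otherwise only if the family seeks care.

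Diarrhoea, rash, feeding difficulty or intercurrent illness may be found at different rates under daily inpatient observation and on caregiver report, even if the true rates are equal. The bias could also run the other way: routine ward charts may leave out minor events that a dedicated day-5 assessment would pick up.

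What is at stake is the non-fatal adverse-event data. The abstract's Discussion paragraph and the Conclusions both look to a finding that these infants can be treated safely after a shorter stay. Any adverse-event table by arm would be read alongside that finding. The protocol already uses independent assessors on matched days to limit measurement bias in the primary outcome, but the article does not extend that protection to adverse events.

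**Working it through.** **Step 1. Set the contacts side by side, from randomisation (day 3) to day 15.**

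| | Control arm | Home arm |
|---|---|---|
| Treating staff | Inpatient for about 5 more days (7 − 2, Table 4) | One scheduled visit, day 5 (Follow-up) |
| Study-specific adverse-event assessment by treating staff named in Follow-up | None; routine procedures | Scheduled outpatient follow-up |
| Family care-seeking | Available after discharge | Available from day 3 |
| Treatment documentation team (Table 2) | Days 4 and 8 | Days 4 and 8 |
| Independent assessor (Outcome assessment) | Days 4, 8, 15 | Days 4, 8, 15 |
| Recorder of adverse events | Treating nurse or physician | Treating nurse or physician |

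The first three rows differ by arm and the last three do not. Table 2 gives the assessor days in a slightly different form from the text, but it applies them to both arms, so the symmetry is not affected.

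**Step 2. Trace the serious-event route.** The assessor documents a serious event after study staff have made contact about it. That step follows someone noticing the event. For non-fatal serious events such as severe diarrhoea or severe rash, noticing can still depend on the arm.

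**Step 3. Illustrate the possible size.** The article gives no adverse-event rate or capture rate, so it has no figure to reproduce. The values below are assumptions.

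Let *r* be the true risk, equal in both arms, and let *d*c and *d*h be the capture probabilities in control and home.

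- Recorded risks: *p*c = *r* × *d*c and *p*h = *r* × *d*h.
- Apparent relative risk: *p*h / *p*c = *d*h / *d*c, whatever *r* is.
- Infants per arm: 5250 / 2 = 2625. After the assumed 10% loss, 2625 × 0.9 = 2362.5, taken as 2362.
- Chance of a spurious two-sided p < 0.05 in the direction of the bias: Φ(*z* − 1.96), with *z* = |*p*c − *p*h| / √{[*p*c(1 − *p*c) + *p*h(1 − *p*h)] / 2362}.

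Worked case: *r* = 5%, *d*c = 0.9, *d*h = 0.7. Then *p*c = 0.045 and *p*h = 0.035. The standard error is √[(0.042975 + 0.033775) / 2362] = 0.0057, so *z* = 0.010 / 0.0057 = 1.75, and Φ(1.75 − 1.96) is about 42%.

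| Capture, control / home | Apparent RR | Spurious p < 0.05, *r* = 2% | *r* = 5% | *r* = 10% |
|---|---|---|---|---|
| 0.9 / 0.8 | 0.89 | 8% | 13% | 23% |
| 0.9 / 0.7 | 0.78 | 19% | 42% | 72% |
| 0.9 / 0.5 | 0.56 | 65% | 96% | about 100% |

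Swapping the two capture rates gives the same chances in the opposite direction, with apparent relative risks of 0.9/0.8 = 1.13, 0.9/0.7 = 1.29 and 0.9/0.5 = 1.80. The effect may therefore be negligible or large, and the article does not fix its sign.

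**The case against.** The strongest reply is that the article plans no between-arm adverse-event comparison. The Outcomes section names no adverse-event outcome, the Data analysis section compares poor clinical outcome only, and adverse events appear as a safety-reporting process. This is correct, and it limits the point to any tabulation by arm that may be made. It does not remove the point, because adverse events are recorded for every enrolled infant and bear on the intended safety conclusion.

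A second reply is that the wording of assessor questions belongs in the forms and the Manual of Operations, which are not shown. That also stands: the absence of a question set from a condensed article is not the finding. The finding is the unequal scheme that the article itself states.

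A third reply is that the adverse-event sentence in Follow-up refers to infants generally, so care-seeking and assessor home visits also apply to control infants once discharged. This is fair. The asymmetry is mainly in the treatment period, and no contrast should be drawn for days 8 to 15, when neither arm has a named treating-staff visit. Nor is the mother the recorder in the home arm. She gives the doses, and the form remains with the treating nurse or physician.

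Finally, unequal observation is inherent in comparing home with hospital care. That is true of clinical contact, but not of research questioning, since the same assessors already see both arms on the same days.

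**Conclusion.** The point holds for non-fatal adverse events. Routes and intensity of collection differ by arm, and a raw comparison is at risk of detection bias whose direction and size the article does not allow one to determine. The figures above rest entirely on assumed capture probabilities and assumed true risks.

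A reader might infer more: that any safety comparison in this trial would show who was watching and not the treatment, or that home treatment would be made to look safer. The documents support neither. Death, signs of critical illness, other serious infection and persisting signs of clinical severe infection are ascertained only by independent assessors, on the same days and with the same windows in both arms. The bias in the remaining events could favour either arm.

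This is a worthwhile and inexpensive improvement to the adverse-event data. It does not affect the validity of the primary comparison.

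**What to change.** In the Follow-up section and the adverse-events section, state two things:

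1. At the existing day 4, 8 and 15 visits the independent assessor asks the same closed set of adverse-event questions in both arms, covering events since the last visit and their onset dates.
2. Any between-arm adverse-event comparison uses these common contacts. Events recorded by treating staff, or at the day-5 hospital visit, are tabulated separately and not pooled into that comparison.

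Serious-event reporting to WHO and the DSMB stays as it is, and clinical care and the visit schedule do not change. If the Manual of Operations already prescribes common questions, a sentence saying so is enough.

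The cost is one short form and a few extra minutes at visits already planned, with no new visits or staff. Caregiver recall of minor events will remain imperfect, but the questions and the timing will be the same in both arms.
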